## 1.3 Summary of the study protocol (Synopsis)

| Study code | VACUM | |
| --- | --- | --- |
| Title of the study | Outcome analysis of the therapy of a radius fracture with  VacoHand®/ forearm splint | |
| Study design | Prospective clinical cross-over study | |
| Planned number of patients: | 50 patients | |
| Duration of the study | Planned beginning of the study:  Planned total duration of the study: | 5/2011  18 months |
| Primary endpoint | The primary endpoint of this study is the patient satisfaction, which is evaluated according to the SF-36 questionnaire. Secondary endpoints are the determination of the DASH Score and of the Neutral-0 Method for the hand as well as for the length of the period of disability. | |
| Inclusion criteria | 18 years of age and AO2.3 A2, A3, B1, B2, B3, C1, C2 fractures which need to be operated with a volar stable plate (2.4mm, 3.5mm, all types) | |
| Exclusion criteria | - Less than 18 years of age - All other AO 2.3 fractures - Open fractures and concomitant injuries - Forearm fractures (except Proc. Styloideus ulnae) - Pathological fractures - Patients, who are unable to support the postoperative treatment by themselves | |

# 2 Introduction

## 2.1 Summary

The distal radius fracture is one of the most common disease patterns in trauma surgery with an incidence of two to three per 1,000 inhabitants. It is a distal fracture of the radius. As it is located close to the wrist, it is commonly referred to as a broken wrist. It occurs in all age groups, but mostly between 6 and 18 years and between 60 and 70 years. The formation mechanism is triggered by a traumatic fall on the extended (Colles fracture), or, more rarely, on the bent wrist (Smith fracture). In children, the distal radius fracture occurs mainly during sports. In adults, however, it is mainly caused by tripping and falling the on uneven or slippery ground. The goal of every therapy, either conservative or operative, is the anatomical reconstruction of the joint surface. Unstable extraarticular and intraarticular fractures are mostly stabilized by plate osteosyntheses, which are mostly fixed to the flexor side, rarely also to the extensor side of the radius close to the wrist. The main advantage of plating is the immediate practice safety, so that the physiotherapy can be started shortly after the postoperative application of the cast,. An early mobilisation can prevent the negative consequences of joint immobilization, like e.g. muscular atrophies, joint immobilisation, tendon conglutination, and capsule contraction. Several studies have demonstrated that the immobilisation provokes a considerable degree of muscular atrophy, especially during the first two weeks. Moreover, it causes metabolic, neurological, and functional adaptations, so that the muscular strength may decrease by half after 4-6 weeks of immobilisation in the cast. A possible solution for this problem is the use of a dynamic vacuum orthesis: It provides the stability of a circular forearm splint, and which therefore allows for an early low-risk increase of load, as well as for a limited mobility in the wrist. Furthermore, the comfort of the patients is increased by the fact that an othesis is less heavy than a splint and can be easily applied by the patient himself after having received an instruction. This enables a regular body care. Besides, the limited mobility of the wrist allows for establishing a more physiological functional image. Moreover, a favourable progress of the postoperative phase could reduce the period of disability in the workforce.

# 3 Goals of the study

The primary endpoint of this study is patient satisfaction, which is measured by the SF-36 questionnaire, after AO2.3 A2, A3, B1, B2, B3, C1, C2 fractures requiring surgery, with a volar angular stable plate (2.4mm, 3.5mm, all types), which are treated postoperatively with a VacoHand^®^/ splint. Targeted surveys relating to pain and the quality of life are carried out. Based on these data, both postoperative treatment methods are compared to each other. Secondary endpoints are the determination of the DASH Score and of the Neutral-0 method for the hand, as well as the duration of the period of disability. In order to achieve these goals, follow-up examinations will be carried out 1, 2, and 6 weeks as well as 6 months after the postoperative treatment.

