# Study design

## 4.1 Design

This study is a prospective clinical cross-over study

.

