## 6.4 Implementation and finalization

The participation at this study is entirely voluntary. A patient can revoke his consent to his participation in the study at any time without stating reasons. Preoperatively, appointments for reevaluation are fixed 1, 2, and 6 weeks postoperatively. Moreover, the patients should know that, after 1, 2, and 6 weeks, as well as after 6 months, he has to fill out a questionnaire and that a clinical control will take place. Only, if a patient agrees to these conditions, he can be included in the study. For those patients, which have agreed to participate in the study, closed envelopes are deposited in the operating theatre. Each envelope contains a piece of paper reading “VacoHand” or “splint”. Depending on the envelope, the patient has to wear initially the VacoHand® or the splint for 1 week in total (unless the operating surgeon indicates otherwise). Then, 1 week postoperative, the splinting is changed from the forearm splinting to the VacoHand® and vice versa.

[figure not shown]

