## Annex:

## Appendix 1: Perimed patient information form

## Appendix 2: SF-36 questionnaire

## Appendix 3: Consent form

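### The protocol text states no recall period for the SF-36, yet devices are swapped after one week; any window over 7 days would dilute the device comparison

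*Protocol*

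**What the plan says.** Section 3 of the Protocol sets the endpoint and its instrument: "The primary endpoint of this study is patient satisfaction, which is measured by the SF-36 questionnaire". The synopsis agrees. Section 4.1 gives the design: "This study is a prospective clinical cross-over study".

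Section 6.4 gives the timing. Of the first device it says "the patient has to wear initially the VacoHand® or the splint for 1 week in total", subject to the surgeon's discretion. It continues: "Then, 1 week postoperative, the splinting is changed from the forearm splinting to the VacoHand® and vice versa". No interval between the devices is described, and the text gives no end date for the second device. On questionnaires, the patient is told that "after 1, 2, and 6 weeks, as well as after 6 months, he has to fill out a questionnaire".

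Section 6.7 says that the questionnaire is annexed, and the annex lists "Appendix 2: SF-36 questionnaire". The annex list names no other questionnaire. Only the title of Appendix 2 is shown. The protocol text itself names no SF-36 version and no recall period.

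**The concern.** A patient-reported score describes the stretch of time that the form asks about. In a cross-over, each score should describe time on one device only. Here the week-1 form can cover at most 7 days on the first device, and the week-2 form at most 7 days on the second. A longer look-back therefore takes in time that does not belong to the device being scored: days before the operation at week 1, and days on the other device at week 2.

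What is at stake is the primary endpoint. A real difference between VacoHand and splint could be shrunk until 50 patients cannot show it. The recall wording is printed on the form the patient completes, so an analysis plan cannot later recover which week an answer described.

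**Working it through.** **Inputs from the Protocol.** The first device is worn from surgery to week 1, the swap is at week 1, and questionnaires fall at weeks 1 and 2 (section 6.4). There are 50 patients (synopsis). The protocol text gives no recall length and no power figures, so there is no planned figure to reproduce.

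**Assumptions.**
- The questionnaire at weeks 1 and 2 is, or includes, the SF-36.
- The second device is worn at least to week 2.
- One recall window of R days applies to the whole score, with R between 7 and 28.
- Every day in the window counts equally.
- The devices are compared by the usual two-period contrast of week-1 and week-2 scores.

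**Formula.** Let A and B be the true scores on the two devices and P the pre-operative score. Let a be the weight of the latest 7 days in the window and b the weight of the 7 days before those.

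- Sequence AB, week 1: y1 = aA + (1 − a)P
- Sequence AB, week 2: y2 = aB + bA + (1 − a − b)P
- AB difference: y1 − y2 = (a − b)A − aB + bP
- BA difference, by symmetry: (a − b)B − aA + bP
- Half the difference between sequences: (a − b/2)(A − B)

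The share of the true difference kept is therefore a − b/2. The difference between the two groups at a single visit is a(A − B) at week 1 and, in absolute size, (a − b)(A − B) at week 2.

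**Numbers with equal day weights.**

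| Recall | Week-1 score | Week-2 score | Share kept, a − b/2 | Group difference kept, week 1 / week 2 |
|---|---|---|---|---|
| 7 days | 100% first device | 100% second device | 1 − 0 = 100% | 100% / 100% |
| 14 days | 50% pre-op, 50% first | 50% first, 50% second | 0.5 − 0.25 = 25% | 50% / 0% |
| 21 days | 67% pre-op, 33% first | 33% pre-op, 33% first, 33% second | 1/3 − 1/6 = 17% | 33% / 0% |
| 28 days | 75% pre-op, 25% first | 50% pre-op, 25% first, 25% second | 0.25 − 0.125 = 12.5% | 25% / 0% |

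**What it does to power (illustration only).** Assume a two-sided 5% test, a normal approximation and an unchanged SD of the within-patient difference. With 50 patients, 80% power corresponds to (1.960 + 0.842)/√50 = 0.396 SD. If that effect is multiplied by 1/4, 1/6 or 1/8, power falls to about 11%, 7.5% or 6.4%. Restoring 80% would need 50 × 16 = 800, 50 × 36 = 1,800 or 50 × 64 = 3,200 patients. A longer window may also lower the SD, so these numbers are an upper illustration.

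**Sensitivity.**
- If patients weight recent days more heavily, a rises and the share kept moves towards 100%.
- If the second device were worn to week 6 and scored there with 28-day recall, the week-6 score would be wholly second device. A week-1/week-6 contrast would then keep (0.25 + 1)/2 = 62.5%, although the week-1 score would still be 75% pre-operative.

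**The case against.** The strongest objection is that the gap may not exist. The form is annexed, and a printed questionnaire carries its own recall wording. If Appendix 2 is a 7-day form, nothing is lost. This stands: a reader might infer that the plan fixes no recall period anywhere, but the document shows only that the protocol text does not state one.

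Second, the week-1/week-2 contrast is an assumption. Questionnaires are also completed at week 6 and month 6, section 3 names no primary time point, and the analysis model may properly sit in an SAP. One week on the second device is likewise inferred from the week-2 visit; section 6.4 states a duration only for the first. Both points stand and limit the size of the loss. They do not remove it, because the week-1 score still follows only 7 days on a device.

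Third, three stronger readings go too far.
- A reader might infer that a long recall puts pre-operative time and both devices into every score. The week-1 score cannot contain the second device, and the week-2 score reaches back before surgery only if recall exceeds 14 days.
- A reader might infer that the primary endpoint would mostly reflect time before surgery. At week 2 the pre-operative share is 0% with 14-day recall and 50% with 28-day recall.
- A reader might infer that a null result would be taken as equivalence. The Protocol sets no equivalence aim or margin.

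**Conclusion.** The concern holds in a conditional form. The protocol text ties its primary endpoint to an instrument whose recall period it does not state, in a design that changes device after one week. Any window over 7 days contaminates the week-1 and week-2 scores. Under equal day weights and a week-1/week-2 contrast, the share of the device difference kept falls from 100% at 7 days to 25%, 17% and 12.5% at 14, 21 and 28 days. These recall lengths are an assumed range, since the document gives none. Recency weighting, or scoring the second device beyond week 2, would make the loss smaller.

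The supportable risk is a falsely null device comparison. It matters because it falls on the primary endpoint and cannot be undone once the forms are completed. If Appendix 2 proves to be a one-week form, all that remains is to say so in the text.

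**What to change.** In section 3, require a one-week-recall SF-36 at the week-1 and week-2 visits, with answers referring to the device worn since surgery (week 1) or since the switch (week 2). Check that the form in Appendix 2 matches, and replace it before the first patient if it does not. The choice of form at week 6 and month 6 can be left to the sponsor.

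The cost is one sentence and possibly a change of form. The small downside is that scores become less comparable with data collected on longer-recall forms.

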# Course of the study and methods of investigation

## 6.1 Clinical examinations

Clinical examinations will be carried out in order to confirm the diagnosis, as a control, and to evaluate the satisfaction of the patients as well as the evolution of pain.

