## 6.3 Planned testing

Regular clinical follow-up examinations and controls as well as targeted surveys regarding pain and patient satisfaction are planned. Based on these data, both methods can be compared to each other.

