## 6.7 Information of the subjects

The information leaflet for the subjects, the questionnaire, and the consent form are annexed.

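### The primary endpoint is labelled patient satisfaction but measured by the SF-36, a general health questionnaire; no satisfaction instrument is named or tied to it

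*Protocol*

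**What the plan says.** The primary endpoint is defined twice, with the same pairing of label and instrument. The synopsis (Section 1.3) reads: "The primary endpoint of this study is the patient satisfaction, which is evaluated according to the SF-36 questionnaire". Section 3 reads: "The primary endpoint of this study is patient satisfaction, which is measured by the SF-36 questionnaire".

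Other parts of the protocol describe what patients will be asked:

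- Section 3, directly after the endpoint definition: "Targeted surveys relating to pain and the quality of life are carried out". The two treatments are then to be compared on these data.
- Section 6.3, in a parallel statement: "targeted surveys regarding pain and patient satisfaction are planned". Again the two methods are to be compared on these data.
- Section 6.1 gives as one purpose of the clinical examinations "to evaluate the satisfaction of the patients as well as the evolution of pain".
- Section 6.4 tells the patient that "after 1, 2, and 6 weeks, as well as after 6 months, he has to fill out a questionnaire".
- Section 6.7 states: "The information leaflet for the subjects, the questionnaire, and the consent form are annexed". The only questionnaire in the annex list is "Appendix 2: SF-36 questionnaire".

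The secondary endpoints are the DASH score, the Neutral-0 measurement of the hand and the length of disability.

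**The concern.** Satisfaction with a device and general health are different quantities. Section 2.1 expects the orthosis to be more comfortable, lighter, easy for patients to apply themselves and better for body care. Patients could value all of these without any visible change in a general health score, particularly in the first weeks after plate surgery, when the fracture and the operation also affect that score. The reverse is possible too: a health score can differ between the devices for reasons unrelated to how satisfied patients are.

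At stake is what the trial may conclude. If the plan is followed as written, an SF-36 result will be published under the name of patient satisfaction. A difference in favour of one device would not show that patients were more satisfied with it, and the absence of a difference would not show equal satisfaction. A statistical analysis plan cannot repair this. It can choose a score, a time point and a model, but it cannot turn answers about health into answers about satisfaction.

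**Working it through.** No arithmetic applies: the protocol gives no figure on this point, and the question is whether label and instrument match. The check reads together every place that mentions satisfaction, quality of life, surveys or questionnaires.

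| Place in the protocol | Construct named | Instrument named | Tied to the primary endpoint? |
| --- | --- | --- | --- |
| 1.3 Synopsis, primary endpoint | satisfaction | SF-36 | yes |
| 3, primary endpoint | satisfaction | SF-36 | yes |
| 3, surveys | pain, quality of life | none | not stated |
| 6.1, examinations | satisfaction, pain | none | not stated |
| 6.3, surveys | pain, satisfaction | none | not stated |
| 6.4, patient's duties | none | one questionnaire, not identified | not stated |
| 6.7, annexed material | none | one questionnaire, not identified | not stated |
| Annex list | none | SF-36 | not stated |

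**Step 1: is the primary endpoint tied to any instrument other than the SF-36?** No. Both definitions name the SF-36 and nothing else.

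**Step 2: does the SF-36 measure satisfaction with the device?** The annexed form is not shown, so this step rests on the general character of the instrument, a generic health and quality-of-life questionnaire. The protocol's own wording agrees with that description, since Section 3 speaks of quality of life immediately after naming the SF-36.

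**Step 3: is the construct used consistently?** No. Sections 3 and 6.3 make the same statement about surveys that serve to compare the two methods. One pairs pain with quality of life, the other pairs pain with satisfaction. The two terms are used as if they were interchangeable.

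**Step 4: is a satisfaction instrument specified elsewhere?** No scale, item or device-specific question is named anywhere. None of the three secondary endpoints is a satisfaction measure. The evaluations announced in Sections 6.1 and 6.3 have no defined content. They may be separate questions, or they may be the SF-36 under another name.

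So the primary endpoint carries a label that its only instrument does not support, and the places where satisfaction is mentioned do not close the gap.

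**A related check: recall.** Section 6.4 places the change of device 1 week after surgery and questionnaires at weeks 1 and 2, so each of these falls 1 week after a device is started. If the annexed form asks about a longer period than that, the week-2 answers would also cover time on the other device. Whether it does cannot be seen from the documents.

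**The case against.** The strongest reply is that the label is merely loose. Section 3 itself speaks of quality of life and compares the treatments on that basis. Section 2.1 expects gains in mobility, muscle function and return to work as well as comfort. On that view the intended endpoint was health-related quality of life all along, and only a word is wrong. This is a fair reading of the intention, and it supports renaming as the leading remedy. It does not remove the defect, because the synopsis and Section 3 both commit the trial to reporting satisfaction.

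A reader might go further than the point made here in two ways. The documents support neither.

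- **That the trial collects no satisfaction measure at all.** Sections 6.1 and 6.3 say that satisfaction will be evaluated. Its absence from the annex list proves little, because the DASH is a named secondary endpoint and no DASH form is listed either. What can be said is that no satisfaction instrument is specified or tied to the primary endpoint.
- **That a long SF-36 recall window would dilute the device contrast by a calculable amount.** Any such figure needs the recall window of a form that is not shown, the length of the second wearing period, which the text does not give, and a primary time point, which the protocol does not name. It would also need an assumption about how patients average over the window.

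It can also be objected that a new single-item rating should not displace an established instrument as the primary endpoint. That objection stands. Patients know which device they are wearing, so such a rating is open to expectation, and making it primary would change the trial's objective.

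**Conclusion.** The point holds in this form: the label and the instrument of the primary endpoint do not match, and the protocol uses satisfaction and quality of life interchangeably for the data behind its main comparison. An SF-36 result could not be reported as higher or equal satisfaction with either device. The defect is in what the protocol states; it is not a detail left for a statistical analysis plan.

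Its size cannot be expressed as a number. It affects the interpretation of the whole primary result, but it says nothing against the SF-36 as a measure of quality of life. The conclusion rests on one assumption, that the annexed form is the usual generic health questionnaire without added questions about the device. If the form does contain such questions, the protocol should name them and say how they enter the primary endpoint.

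**What to change.** 1. In the synopsis and Section 3, rename the primary endpoint *health-related quality of life (SF-36)*.
2. Reconcile Sections 1.3, 3, 6.1 and 6.3, so that each says which construct is assessed and with which instrument. Where Sections 6.1 and 6.3 mean the SF-36, say so; where they mean something else, name it.
3. Base no claim about satisfaction on the SF-36.
4. If satisfaction is to remain a question the trial answers, add one rating of the device worn during the past week, for example on a 0-10 scale. Take it at the planned week-1 visit, before the switch, and at the planned week-2 visit, and report it as a separate endpoint.
5. Check that the recall window of the annexed SF-36 form suits an assessment 1 week after each device is started.

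Items 1 to 3 cost only protocol wording. Item 4 adds one question at two visits already scheduled; its small downside is that it is a single-item rating given by patients who know which device they wear. It needs to be in place before data are collected, because no later analysis can supply answers to a question that was not asked. Item 5 is a check of a form the sponsor already has.

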# Study design

## 4.1 Design

This study is a prospective clinical cross-over study

.

## 4.2 Duration of the study

The duration of the study, including data collection, should not exceed 18 months.

# Study population

## 5.1 Recruiting

The recruting of patients takes place at the Clinic for Trauma and Restorative Surgery, BG Klinik Tübingen. The patients will be infformed on the study, will receive the information leaflet and have a consultation, in which all unresolved issues will be clarified.

## 5.2 Inclusion criteria

- At least 18 years old
- AO2.3 A2, A3, B1, B2, B3, C1, C2 fractures requiring surgery, which have been treated with a volar angular stable plate (2.4mm, 3.5mm, alle types)
- Soft tissue G0, G1
- Patients have to be able to actively support the postoperative treatment.

**AO classification of the distal radius fracture:**

[figure not shown]

Copied from Thieme „via medici“

#### **Closed fractures (Soft tissue classification):**

- Grade 0: No or insignificant soft tissue injury, indirect trauma, simple fracture
- Grade I: Superficial abrasion or contusion by fragment pressure from the inside, simple to moderate fracture
- Grade II: Deep, dirty abrasion, contusion by direct trauma, imminent compartment syndrome, moderate to severe fracture
- Grade III: Extensive contusion or destruction of the musculature, subcutaneous avulsion of the skin, manifest compartment syndrome, injury of a main vessel

